## SCHEDULE OF EVENTS: SAMPLE COLLECTION FOR TRACT STUDY

[figure not shown]

Escalating doses of autologous expanded Tregs (TRACT) will be administered to the next cohort of patients if there are no observed serious adverse events within 30 days of TRACT infusion as follows:

Tier 1:  $0.5 \times 10^9$  total expanded Tregs (n=3)

Tier 2:  $1 \times 10^9$  total expanded Tregs (n=3)

Tier 3:  $5 \times 10^9$  total expanded Tregs (n=3)

Tier 4:  $8 \times 10^9$  total expanded Tregs (n=3)

Patients will be monitored at various time points, as described above for evidence of donor-specific transplantation tolerance using in vitro analyses, specifically mixed-leucocyte reaction assays (MLR). Graft function will be monitored clinically in the standard fashion. The overall goal for this phase I study is to demonstrate the safety of TRACT administration in kidney transplant recipients, and lay the foundation for a subsequent phase 2 trial. If we are successful, this approach could have for a transformative effect upon the field of solid organ and cellular transplantation.

The clinical site for recruitment, enrollment, and treatment of patients will be Northwestern Memorial Hospital. The Principal Investigator is part of a team with the most active living donor renal transplant program in the nation, with more than 160 such transplants performed in 2011. There already exists a robust infrastructure for combined therapeutic cell transfer (stem cell) and solid organ transplantation with two protocols for living donor renal transplants + HSC having been active at Northwestern for almost 5 years; [name], the IND sponsor and co-investigator, serves as PI or co-PI on these trials (50, 51).

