### TREATMENT SCHEMA

EXPERIMENTAL: TRACT (N=12)  
AUTOLOGOUS TREG INFUSION

Kidney transplantation using standard of care immunosuppressive agents will be performed, followed by intravenous infusion of autologous, expanded Tregs (TRACT) at day 60 after transplantation. Subjects will be administered only one dose of Treg at the specified dose level. Cell infusions will be escalated in the absence of adverse events within 30 days of infusion using the following schema:

Tier 1:  $0.5 \times 10^9$  total expanded nTregs (n=3)

Tier 2:  $1 \times 10^9$  total expanded nTregs (n=3)

Tier 3:  $5 \times 10^9$  total expanded nTregs (n=3)

Tier 4:  $8 \times 10^9$  total expanded nTregs (n=3)

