#### 4.1 General Design

This is an open label, single-center phase I study of TRACT in living donor renal transplant recipients. This safety portion of this study will continue for six months but the patients will be followed for up to 60 weeks. Participants will receive “standard of care” immune suppression, living donor kidney transplantation and TRACT. Prior to the kidney transplant, blood will be collected for immunophenotypic analysis of circulating leukocytes by flow cytometry, as well as functional immune assays. **Dose escalation of nTregs will be based upon the absence of infusion related side effects and specific adverse events (subsequent rejection episodes, allosensitization, development of opportunistic infection) within 30 days of infusion.**

Patients will undergo living donor kidney transplantation using immunosuppression based upon the standard of care regimen using alemtuzumab and the avoidance of oral corticosteroids (46, 47). This immunosuppressive regimen has been used for more than a decade at Northwestern in more than 2000 kidney transplant recipients. All patients will receive two doses of alemtuzumab (Campath-1H, 30mg); one at the time of renal transplant, and one on post-operative day two to achieve peripheral T-cell depletion. Intravenous glucocorticoids will be administered prior to Campath administration to limit cytokine release syndrome in association with this monoclonal antibody, and continued for the first two days post-transplant. Thereafter, steroids will not be used for immunosuppression. All transplant recipients will be started on oral immunosuppressive therapy with MPA and tacrolimus prior to transplant. After 30 days, patients will be converted to the combination of Sirolimus and MPA, as the inhibition of IL2 production by CNIs would impair the survival of infused expanded Tregs.

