## **7.4 Dose Limiting Toxicity (DLT) Determination in the Study**

This is an open-label, single arm, dose escalation- de-escalation, phase I safety study which will examine the feasibility and safety of infusing autologous regulatory T cells (Tregs) into patients who have received a living donor kidney transplant. Tregs will be administered approximately 60 days post kidney transplantation.

According to the phase I dose escalation/de-escalation study design described below. The 4 dose levels are:  $0.5 \times 10^9$ ,  $1 \times 10^9$ ,  $5 \times 10^9$ ,  $8 \times 10^9$  Treg cells. All patients will be observed for a minimum of four hours following infusion and cell related toxicities monitored for the next three weeks. Patients with grade 3 or 4 toxicity during the infusion will have their cellular administration discontinued immediately and the event noted as a dose-limiting toxicity.

Adverse event information from the infusion will be used to determine whether the next subject within each cohort will receive the dose of cells associated with that dose level. The PI, IND Sponsor, IND Medical Monitor and study co-investigators will review toxicity reports and recommend whether or not it is safe to proceed at this dose level for the next patient. The next patient within a dose level will only be administered Treg after the first patient has been followed for at least 21 days and no evidence of dose limiting toxicity has been seen. The dose level for a given patient and the progression of doses from one cohort of patients to the next will be adjusted based on adverse events.

Adverse event information from the infusion will be used to determine whether or not dose escalation or de-escalation to the next level will occur. Adverse events will be graded using the Common Toxicity Criteria for Adverse Events, version 4.0e (NCI-CTCAE v4).

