A dose-limiting toxicity (DLT) is defined as a clinically significant adverse event or abnormal laboratory value assessed as unrelated to the kidney transplant, intercurrent illness, or concomitant medications and occurring during the first 3 weeks after administration of the first dose that meets any of the following criteria: grade 3 or 4 non-hematologic toxicity (except for electrolyte disturbances responsive to correction measures within 48h, diarrhea, nausea and vomiting that responds to standard medical care, rash  $\geq$  Grade 3 that response to supportive care, infusion relation reaction that are responsive to supportive care, infections and infectious complications related to patients neutropenia, elevated creatinine  $<3.5 \times$  upper limit of normal, elevated AST  $< 8 \times$  upper limit of normal, elevated ALT  $<8 \times$  upper limit of normal, elevated bilirubin  $< 5 \times$  upper limit of normal, elevated PTT  $< 3.5 \times$  upper limit of normal).

Dose escalation will only occur after patients, at a given dose level, have been followed for at least 21 days and no evidence of dose limiting toxicity has been seen. The dose level for a given patient and the progression of doses from one cohort of patients to the next will be adjusted based on adverse events. If a patient is discontinued due to concurrent illness unrelated to toxicity or organ rejection before they reach the end of the treatment cycle (21 days after the infusion), an additional patient will be enrolled at that same dose level.

| No. of Patients with DLT at a Given Dose Level | Escalation Decision Rule                                                                                                                                                                                                                                              |
|------------------------------------------------|-----------------------------------------------------------------------------------------------------------------------------------------------------------------------------------------------------------------------------------------------------------------------|
| 0 out of 3                                     | Enter patient(s) at the next dose level.                                                                                                                                                                                                                              |

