| $\geq 2$                                       | Dose escalation will be stopped. This dose level will be declared the maximally administered dose (highest dose administered). Three additional patients will be entered at the next lowest dose level if only 3 patients were treated previously at that dose level. |
| 1 out of 3                                     | Enter at least 3 more patients at this dose level. 
 
If 0 of these 3 patients experience DLT, proceed to the next dose level.
 
                                                                                         |

|                                                                          |                                                                                                                                                                                                                                                                                                                      |
|--------------------------------------------------------------------------|----------------------------------------------------------------------------------------------------------------------------------------------------------------------------------------------------------------------------------------------------------------------------------------------------------------------|
|                                                                          | 
 
If 1 or more of this group suffer DLT, then dose escalation is stopped and this dose is declared the maximally administered dose. Three additional patients will be entered at the next lowest dose level if only 3 patients were treated previously at that dose.
 
 |
| ≤ 1 out of 6 at highest dose level below the maximally administered dose | This will be the Maximum Tolerated Dose (MTD). At least 6 patients will be entered at this dose.                                                                                                                                                                                                                     |

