#### **Serious Adverse Event**

Adverse events are classified as serious or non-serious. A *serious adverse event* is any AE that is:

- fatal
- life-threatening
- requires or prolongs hospital stay
- results in persistent or significant disability or incapacity
- a congenital anomaly or birth defect
- an important medical event

Important medical events are those that may not be immediately life threatening, but are clearly of major clinical significance. They may jeopardize the subject, and may require intervention to prevent one of the other serious outcomes noted above. For example, drug overdose or abuse, a seizure that did not result in in-patient hospitalization, or intensive treatment of bronchospasm in an emergency department would typically be considered serious.

**Unrelated** ---Any reaction that is clearly due to extraneous causes AND that is likely to have been produced by the subject's clinical state or other modes of therapy administered to the subject.

**Unlikely** ---Any reaction that does not follow a reasonable temporal sequence from the study intervention (in this case TRACT infusion) OR that is likely to have been produced by the subject's clinical state or other modes of therapy administered to the subject.

**Possible** ---A reaction that follows a reasonable temporal sequence from the study intervention (in this case infusion of TRACT) OR that follows a known response pattern to the suspected drug AND that could not be reasonably explained by the known characteristics of the subject's clinical state or other modes of therapy administered to the subject.

**Probable** ---A reaction that follows a reasonable temporal sequence from the study intervention (in this case TRACT infusion) OR that follows a known response pattern to the suspected drug AND that could not be reasonably explained by the known characteristics of the subject's

clinical state or other modes of therapy administered to the subject *AND* improves with the reduction in dose or cessation of the intervention.

**Definite**---A reaction that follows a reasonable temporal sequence from the study intervention (in this case TRACT infusion and toxicities occurring during the first 24 hours post-infusion) *AND* that follows a known response pattern to the suspected therapy

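### Four dose-escalation rules are stated and none is named as governing; three allow no events over 30 days, while the 3+3 table allows 1 DLT in 6 over 21 days and contradicts its own text

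*Protocol*

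**What the plan says.** The Protocol states the condition for moving to the next tier in four places.

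1. **Treatment Schema:** "Cell infusions will be escalated in the absence of adverse events within 30 days of infusion using the following schema". Read literally, any adverse event counts.
2. **Section 4.1, opening paragraph (in bold):** escalation "will be based upon the absence of infusion related side effects and specific adverse events", namely rejection, allosensitization and opportunistic infection, within 30 days.
3. **Section 4.1, under the Schedule of Events:** the higher dose "will be administered to the next cohort of patients if there are no observed serious adverse events within 30 days of TRACT infusion".
4. **Section 7.4:** a 3+3 table based on DLTs. A DLT must be "assessed as unrelated to the kidney transplant, intercurrent illness, or concomitant medications and occurring during the first 3 weeks", and must meet grade 3-4 criteria with a list of exemptions. With 0 of 3 DLTs the next tier opens. With 1 of 3, three more patients are entered, and then: "If 0 of these 3 patients experience DLT, proceed to the next dose level".

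The text of 7.4 around that table is stricter than the table. It permits escalation only after patients at the level "have been followed for at least 21 days and no evidence of dose limiting toxicity has been seen". Within a level, "The next patient within a dose level will only be administered Treg after the first patient has been followed for at least 21 days", again with no DLT seen.

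The Study Summary and Treatment Schema give 12 subjects, three per tier. Section 1.9 plans for up to 20 consents.

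**The concern.** Whether to raise the dose is the main decision in this trial. The four rules differ in which events count, in the window (30 or 21 days) and in the number tolerated (none, or 1 in 6). No sentence ranks them.

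The second problem lies inside 7.4. Its text closes the route that its table opens: after 1 DLT in 3, the condition that no DLT has been seen at that level can never be met. If the DLT is in the first patient, the text does not even allow the second to be treated, so the 1-of-3 row cannot be reached.

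The highest dose given, and so the safety statement carried into the planned phase 2 trial, would depend on which section the team applied. The number of patients treated is also open, because the table can expand every tier from 3 to 6.

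**Working it through.** **Stated size.** 4 tiers × 3 patients = 12, as the Protocol says.

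**The rules side by side**

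| Source | Events that block | Window | Tolerated |
|---|---|---|---|
| Treatment Schema | any adverse event | 30 days | 0 |
| 4.1, opening paragraph | infusion side effects, rejection, allosensitization, opportunistic infection | 30 days | 0 |
| 4.1, Schedule of Events | serious adverse events (SAEs) | 30 days | 0 |
| 7.4 text | DLTs | at least 21 days | 0 |
| 7.4 table | DLTs | 21 days | 1 of 6 |

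**Same data, different decisions**

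- An unplanned admission on day 10 that is an SAE (Section 9.1 includes an event that "requires or prolongs hospital stay") and is attributed to the transplant blocks escalation under the Schema and the 4.1 SAE rule. It is not a DLT.
- A rejection on day 25 blocks under the Schema and the opening paragraph of 4.1. It falls after the DLT window, so 7.4 does not count it.
- One DLT in the first three patients and none in the next three clears the tier under the 7.4 table and blocks it under the 7.4 text.

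**Illustrations.** The documents give no event rates, so 5%, 10% and 20% are assumptions.

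(a) *SAE rule against the table.* Let q be the risk of an SAE within 30 days, with no DLTs. P(at least one in 3) = 1 − (1 − q)³.
- q = 5%: 1 − 0.95³ = 0.143
- q = 10%: 1 − 0.90³ = 0.271
- q = 20%: 1 − 0.80³ = 0.488

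The table blocks none of these cohorts.

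(b) *7.4 text against the 7.4 table.* Let p be the DLT risk. P(1 of 3, then 0 of 3) = 3p(1 − p)² × (1 − p)³ = 3p(1 − p)⁵. The chance of clearing all three steps to Tier 4 is [(1 − p)³]³ under the text and [(1 − p)³ + 3p(1 − p)⁵]³ under the table, with the same p at every tier.

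| p | Text and table disagree, per tier | Reach Tier 4: text | Reach Tier 4: table |
|---|---|---|---|
| 5% | 0.116 | 0.630 | 0.922 |
| 10% | 0.177 | 0.387 | 0.744 |
| 20% | 0.197 | 0.134 | 0.356 |

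(c) *Number treated under the table.* The maximum is 4 × 6 = 24. All cohort paths were enumerated exactly with constant p. De-escalation adds 3 patients where only 3 had been treated. The result depends on whether a top tier cleared at 0 of 3 stays at 3 patients or is filled to 6, since the last row of the table asks for at least 6 at the maximum tolerated dose (MTD).

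| p | P(N > 12), top tier 3 | P(N > 12), top tier 6 | P(N > 20), top tier 3 | P(N > 20), top tier 6 |
|---|---|---|---|---|
| 5% | 0.401 | 0.942 | 0.010 | 0.041 |
| 10% | 0.521 | 0.803 | 0.036 | 0.090 |
| 20% | 0.399 | 0.467 | 0.055 | 0.092 |

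**Timing.** 30 − 21 = 9 days. A cohort released at day 21 under 7.4 moves on before any of the 30-day rules can be judged.

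**The case against.** The best defence is that 7.4 is plainly the operative section. It is the most detailed, it announces the design to be followed, and only its table is presented as a decision rule; the other three statements are one-sentence overviews. A reader could reasonably take it that way, but the Protocol never says so, the rule in 4.1 is set in bold, and choosing 7.4 leaves the conflict between its text and its table.

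Other points carry some weight:

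- **Window.** The 21 days are a minimum, so a review at day 30 would satisfy every rule on timing. The event lists and tolerated counts would still differ.
- **Applying all rules together.** Read literally, the Schema makes escalation through the 1-of-3 row impossible, because every DLT is an adverse event. If the Schema is shorthand for the SAE rule, that argument weakens: a DLT could be a grade 3 laboratory value that is neither an SAE nor one of the events named in 4.1. The 7.4 text would still close the row, and three different criteria would remain.
- **Hospitalisation.** Section 9.1 exempts some admissions (elective or diagnostic procedures for a preexisting condition, and treatment of the target disease without worsening). The day-10 example therefore needs an admission outside those exemptions.
- **Safeguards.** The investigator, IND sponsor and medical monitor review each step, and Section 7.5 can halt the study for certain severe events within 30 days. These limit risk to patients, but the reviewers still have no single rule to apply.
- **Sample size.** Exceeding 20 treated patients is unlikely on the assumed rates (at most about 9% on either reading), so the consent ceiling is secondary.

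**Conclusion.** The concern holds and must be fixed before the rules are applied. The differences that come straight from the Protocol need no assumption: 0 against 1 of 6 tolerated, 30 against 21 days, three different 30-day event lists, a table contradicted by its own text, and a stated size of 12 against a possible 24.

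The probabilities only show that the disagreement would not be rare. They rest on assumed risks of 5% to 20%, independence between patients and, where several tiers are combined, one constant risk. The probabilities of exceeding 12 or 20 patients also depend on how the requirement for 6 at the MTD is read; filling the top tier to 6 raises them.

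**What to change.** - Keep one escalation rule, in Section 7.4, giving the event list, the window and the allowed count. Which events to include is for the sponsor to decide.
- Replace the escalation sentences in the Treatment Schema and both places in Section 4.1 with a reference to 7.4.
- Make the 7.4 text on the next patient and on the next tier agree with the table, including what happens when the first patient at a level has a DLT.
- Set the cohort review no earlier than the longest window in the rule. That is day 30 if rejection, allosensitization and opportunistic infection stay in.
- If the table is kept, say whether a top tier cleared at 0 of 3 is filled to 6. If it is not, state the size as 12 when no tier expands and up to 24 otherwise; if it is, clearing the top tier takes 15 to 24. Bring the consent ceiling of 20 into line.

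The cost is Protocol wording plus, if review moves from day 21 to day 30, up to 9 days per step, or 3 × 9 = 27 days over three steps. Keeping the table also means planning for up to 24 treated patients and more than 20 consents.

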## 4.2 Primary Safety Endpoint

The primary safety endpoint is the evaluation of cellular related toxicities immediately and within 24 hours post-infusion of TRACT. Since TRACT is being administered to promote immunosuppression and prevent rejection, specific adverse events (subsequent rejection episodes, allosensitization, development of opportunistic infection) within 30 days of infusion will be monitored.

## 5 Subject Selection

The target population is adult recipients of immediately functioning living donor renal allografts. Immediate function will be defined as the absence of the need for hemodialysis in the first week following renal transplantation.

### 5.1 Inclusion Criteria

1. Patients who are males or females age 18-65 years.
2. Donor age 18-65 years.
3. No prior organ transplant.
4. Patients who are single-organ recipients (kidney only).
5. Women who are of childbearing potential must have a negative serum pregnancy test before transplantation and agree to use a medically acceptable method of contraception throughout the treatment period.
6. Subject (recipient) is able to understand the consent form and give written informed consent.

### 5.2 Exclusion Criteria

1. Known sensitivity or contraindication to Sirolimus, tacrolimus or MMF.
2. Patient with significant or active infection.
3. Patients with a positive flow cytometric crossmatch using donor lymphocytes and recipient serum.
4. Patients with PRA >20%.
5. Patients with current or historic donor specific antibodies.
6. Body Mass Index (BMI) of < 18 or > 35.
7. Patients who are pregnant or nursing mothers.
8. Patients whose life expectancy is severely limited by diseases other than renal disease.
9. Ongoing active substance abuse, drug or alcohol.
10. Major ongoing psychiatric illness or recent history of noncompliance.
11. Significant cardiovascular disease (e.g.):
  - Significant non-correctable coronary artery disease;
  - Ejection fraction below 30%;
  - History of recent myocardial infarction.
12. Malignancy within 3 years, excluding nonmelanoma skin cancers.
13. Serologic evidence of infection with HIV or HBVsAg positive.
14. Patients with a screening/baseline total white blood cell count  $\leq 4,000/\text{mm}^3$ ; platelet count  $\leq 100,000/\text{mm}^3$ ; triglyceride  $\geq 400$  mg/dl; total cholesterol  $\geq 300$  mg/dl.
15. Investigational drug within 30 days prior to transplant surgery.

14. Anti-T cell therapy within 30 days prior to transplant surgery.

